# TEAM-UP for quality: a cluster randomized controlled trial protocol focused on preventing pressure ulcers through repositioning frequency and precipitating factors

**DOI:** 10.1186/s12877-018-0744-0

**Published:** 2018-02-20

**Keywords:** Pressure ulcer, Pressure injury, Prevention, Nursing, Repositioning

## Abstract

**Background:**

Pressure ulcers/injuries (PrUs), a critical concern for nursing homes (NH), are responsible for chronic wounds, amputations, septic infections, and premature deaths. PrUs occur most commonly in older adults and NH residence is a risk factor for their development, with at least one of every nine U.S. NH residents experiencing a PrU and many NHs having high incidence and prevalence rates, in some instances well over 20%. PrU direct treatment costs are greater than prevention costs, making prevention-focused protocols critical. Current PrU prevention protocols recommend repositioning residents at moderate, high, and severe risk every 2 h. The advent of visco-elastic (VE) high-density foam support-surfaces over the past decade may now make it possible to extend the repositioning interval to every 3 or 4 h without increasing PrU development. The TEAM-UP (Turn Everyone And Move for Ulcer Prevention) study aims to determine: 1) whether repositioning interval can be extended for NH residents without compromising PrU incidence and 2) how changes in medical severity interact with changes in risk level and repositioning schedule to predict PrU development.

**Methods:**

In this proposed cluster randomized study, 9 NHs will be randomly assigned to one of three repositioning intervals (2, 3, or 4 h) for a 4-week period. Each enrolled site will use a single NH-wide repositioning interval as the standard of care for residents at low, moderate, and high risk of PrU development (*N* = 951) meeting the following criteria: minimum 3-day stay, without PrUs, no adhesive allergy, and using VE support surfaces (mattresses). An FDA-cleared patient monitoring system that records position/movement of these residents via individual wireless sensors will be used to visually cue staff when residents need repositioning and document compliance with repositioning protocols.

**Discussion:**

This study will advance knowledge about repositioning frequency and clinically assessed PrU risk level in relation to PrU incidence and medical severity. Outcomes of this research will contribute to future guidelines for more precise preventive nursing practices and refinement of PrU prevention guidelines.

**Trial registration:**

Clinical Trial Registration: NCT02996331.

## Background

Pressure ulcer/injury (PrU) prevention remains a challenge within the nursing home (NH) environment [1, 2]. A PrU is any skin lesion over a bony prominence resulting from prolonged exposure to pressure that causes capillary occlusion and eventual tissue necrosis. Most PrUs are avoidable, but those that do develop are associated with complications (e.g., chronic wounds, amputations, septic infections, and premature deaths) [3] and with overall deterioration in prognosis, compromising both a patient’s health status and quality of life. Estimated annual treatment costs ($9.1–11.6 billion in the US [4]) are greater than prevention costs [4–8], even without considering other costs to the individual and healthcare system (outpatient visits, work loss, and lawsuits), thus making prevention a priority [9].

Residence in a NH puts individuals at risk of developing PrUs [8], and the limited mobility prevalent among NH residents [10] increases the intensity and duration of pressure exposure – two factors leading to PrU development [11]. The severity of illness, including signs, symptoms, physiologic parameters, and disease factors, also affects the body’s response to pressure exposure and possibly increases risk for PrU development. A universally accepted approach to PrU prevention is to minimize pressure exposure through frequent moving/repositioning (hereafter referred to as repositioning) [12, 13] for residents clinically assessed as at-risk (typically Braden Scale© score ≤ 18).

Over the last decade, NH PrU incidence rates have declined from 11% [14] to 7.8% [15]. This decline can be attributed to the advent of viscoelastic (VE) high-density foam support surfaces that reduce pressure intensity by redistributing point pressure. VE surfaces make longer intervals between repositioning possible for at-risk residents confined to bed or chair [16]. However, in order to further improve PrU prevention approaches [17], we must determine 1) how frequently repositioning needs to occur in order to prevent PrU development, and 2) how residents’ medical severity (severity of illness), risk level (clinically assessed risk determined by the Braden Scale©), and repositioning frequency affect PrU development individually or in combination. It is not known whether a 2, 3, or 4 h time interval for repositioning of residents is most effective in preventing PrUs.

Current PrU prevention repositioning protocols (derived from two small 1962 studies [18]) recommend repositioning residents at moderate, high, and severe-risk every 2 h. With VE surfaces, it may be possible to reduce repositioning frequency by extending the repositioning interval (time elapsed between scheduled repositioning of residents) from 2 to 3 or even 4 h without an increase in PrU development. In the last decade, only two studies have examined repositioning protocols. One study reported fewer PrUs in residents using VE surfaces with a 4-h repositioning interval than in residents who used non-VE surfaces with more frequent repositioning [19, 20]. The second study, Turning for Ulcer ReductioN (TURN) trial, found no significant differences in PrU incidence between 2, 3, or 4-h repositioning intervals in a sample of moderate and high-risk residents using VE surfaces. In these two studies, 90% of all new PrUs occurred within the first 15 days [20]. However, new PrUs cannot be attributed to any single factor [21], and these analyses did not comprehensively examine changes in residents’ PrU risk levels or their physiological and disease factors (medical severity).

We will examine the effects of repositioning frequency (using assigned repositioning intervals of 2, 3, or 4 h) on residents at low, moderate, and high risk of developing PrUs (Braden Scale score 10-23) and will explore the effects of risk level and medical severity individually and in combination over a 4-week intervention period. Residents deemed to be at low risk are not commonly studied, but they too develop PrUs [2, 14–16] and are therefore included in this study. An FDA-cleared patient monitoring (PM) system using individual wireless tri-axial accelerometer sensors will record resident position and movement, automate repositioning schedules, provide visual cues to nursing staff [22] via electronic display screens at the nursing station and unit hallway(s) that indicate when each resident needs repositioning, and confirms completion of repositioning. This system provides a timestamp that repositioning occurred and addresses concerns about nursing electronic medical record (EMR) documentation compliance.

The specific aims of the TEAM-UP (Turn Everyone And Move for Ulcer Prevention) study are to:Aim 1: Determine differences in the incidence of new pressure ulcers (PrU) in nursing home (NH) residents at low, moderate, and high risk using VE support surfaces and repositioned at intervals of 2, 3, or 4 h, in nine randomly assigned NHs over a 4-week period, using the patient monitoring (PM) system to determine movement.Aim 2: Determine how medical severity components (as measured by a modified Comprehensive Severity Index [23, 24]), changes in clinically assessed risk level (low, moderate, high as measured by the Braden Scale© [25]), assigned repositioning intervals, and their interactions are associated with development of PrUs, controlling for resident demographics.Exploratory Aim: Evaluate PrU prevention intervention approaches in NH groups repositioned at 2, 3, or 4-h by: 1) comparing the intervention resource costs (VE support surfaces, PM system service/sensor use, fixed and variable labor costs for training and repositioning) and incremental cost-effectiveness ratio of cost per % reduction in PrUs, and 2) exploring staff and resident satisfaction with intervention approach.

### Significance

PrUs occur most commonly in older adults [6], and NH residence is a risk factor [8] for development. At least one of every nine U.S. NH residents will experience a PrU [14, 26] and many NHs have high incidence and prevalence rates, in some instances well over 20% [27, 28]. The estimated cost of treating PrUs ranges from $21,000–152,000 per PrU [29]. Effective prevention can reduce PrU incidence and avoid treatment costs while improving resident satisfaction, safety, and quality of life. Residents identified as moderate- or high-risk (who comprised 22–28% and 56–57% respectively of the NH population in two recent studies [12, 30]) are considered most likely to develop PrUs; however, low-risk NH residents also develop PrUs [19, 28, 31] and must be considered in any comprehensive prevention approach. PrUs are challenging to address, given the variations in NH size, staffing, and resident diversity, but creating cost-effective solutions is imperative because1 in every 5 adult Americans (some 72 million) will be > 65 years old by 2030 and PrUs could increase exponentially [6].

PrUs remain a multifactorial problem, although the advent of innovative products (e.g., VE support surfaces) has minimized some risk. In order to further reduce PrU incidence, it is important to both 1) test and challenge current prevention protocols to identify a gold standard, and 2) understand the intersection of multiple contributing factors to PrUs to identify additional opportunities for improvement. Improving prevention protocols is critical on multiple levels (i.e., individual, department, facility, society) given the cost of treating PrUs, the direct impact on both staff and residents, and the fact that overall costs of delivering prevention protocols is less than treatment costs.

The TEAM-UP study challenges the idea that repositioning must be completed every 2 h to best prevent the onset of PrUs. It builds on prior evidence from an intervention study [19, 20] showing that repositioning intervals may be extended from every 2 h to every 3 or 4 h without increasing PrU incidence, and attempts to expand the evidence base for PrU prevention by determining how residents’ medical severity, clinically assessed PrU risk level, and assigned repositioning interval affect PrU development individually or in combination. TEAM-UP extends previous study periods [19, 20] to 4-weeks (28 days) to help determine the optimal resident repositioning interval, and will: 1) place all NH residents on VE (high-density foam) support surfaces to avoid point pressure and redistribute pressure, so as to enable longer periods between repositioning; 2) enroll residents at low risk for PrU development in addition to those identified as moderate or high risk; 3) use a PM system with individual wireless sensors to track repositioning compliance with time-stamped documentation and provide repositioning reminders, while also providing automatic feedback for individual nursing staff and the team to improve communication; and 4) monitor fluctuations in resident characteristics and risk levels, which may be associated with development of PrUs. The study intervention will be carried out by NH staff in real-life practice conditions with protocol and training support, rather than by an external intervention team. The impact of the intervention on the occupational subculture of the nursing staff will be explored, as will the perspectives of both nursing staff and residents. Nurse champions will be trained to support staff as resources for protocol implementation and the use of the PM system and sensors.

## Methods

The TEAM-UP study is a cluster randomized clinical trial with facility-level use of an assigned repositioning interval as the primary intervention and will be conducted at 9 NHs that are all using VE support surfaces. Each participating NH will be randomly assigned to one of three intervention arms. Each arm will have 3 NHs with each NH using a single, NH-wide repositioning interval at either 2, 3, or 4 h as standard of care during the 4-week intervention period. Randomization will occur at the facility level. The sequence in which the repositioning intervals are to be implemented will be randomly ordered and, then assigned to NHs inclusive of each arm of NHs. Thus, 3 clusters of 3 NHs are created with randomly sequenced repositioning intervals.

A secondary cluster is created within each NH as the NH implements its standard risk assessment protocol; residents will be clinically categorized forming clusters by level of risk for developing a new PrU. Level of risk categorization into 3 groups is defined by a Braden score of low (15–18), moderate (13–14), or high (10–12) [32]. All eligible residents will wear a wireless triaxial accelerometer sensor throughout the intervention as part of the NH’s standard of care. Residents may refuse the sensor and can decline to move when prompted by staff as part of their right to refuse care (see Fig. 1). This pragmatic approach offers a unique opportunity to study a single NH-wide repositioning schedule, thus avoiding the potential for staff confusion associated with resident-level random assignment to repositioning intervals, which would require staff to simultaneously execute multiple turning schedules.

**Fig. 1 Fig1:**
[figure not shown]
Flowchart for study protocol manuscript

Medical severity components and clinically assessed risk level will be extracted from the EMR and examined for assessment-to-assessment change, thus allowing identification of medical severity components associated with development of a new PrU. We will use intervention resource cost elements (VE surfaces, PM system and sensor service, fixed and variable labor costs for training and repositioning) to assess implementation cost and calculate a cost-effectiveness ratio per % PrU reduction. NH nursing staff will be asked to complete a nursing culture assessment web-based survey administered electronically at their NH pre- and post-intervention. Focus groups will be conducted using semi-structured questions framed according to the Diffusion of Innovation model to gather/assess NH staff and resident perspectives of each group’s satisfaction regarding the repositioning interval and challenges experienced in use of the PM system.

Additional information is available on the study website (https://teamup.nursing.duke.edu).

We are funded to conduct this study from 07/01/2016 to 03/31/2021. We have completed implementation in 3 of the 9 nursing homes and additional study data collection and analyses will be completed by 03/31/2021.

### Sample, setting, recruitment

#### NH sample

Researchers established a collaboration with a United States, for-profit, Medicare-certified, intermediate and skilled NH system with > 450 NHs in over 30 states. A convenience sample of 9 NHs will be selected from volunteer facilities within the system if they have > 100 beds and are using viable VE mattresses examined 2 months prior to intervention implementation, and have full EMR use that includes activity of daily living (ADL) documentation and laboratory and radiology electronic results. Participating NHs must agree to implement the patient monitoring system technology with a NH-wide repositioning protocol, and agree to a mandatory nursing staff in-service training provided by the research team. Full-time and part-time nursing staff (RNs, LPNs, CNAs) working clinically with residents will participate in an NH-mandated education session to explain the study protocol and prepare them regarding PM system use. NH’s will be assigned in random order to a repositioning interval.

The NH will give all its residents/family an information sheet that explains the study and NH-wide adopted repositioning protocol and informs them of their right to refuse care and/or request a more frequent repositioning interval. The information sheet will also explain risks, benefits, and what is involved in participation.

#### Resident sample

All residents (≥ 18 years old) using a VE mattress (support surface) who are without PrUs and adhesive allergy and are clinically assessed as low, moderate, or high risk for new PrU development will participate in their respective NH-wide repositioning frequency protocol and receive standard PrU prevention care.

NH resident participants will include those residents at the time of study initiation and any residents newly admitted during the 4-week study period. All individuals who are NH residents for a minimum of 3 days and meet inclusion criteria will be included in data analyses, because superficial PrUs have been reported to occur within several hours to days following NH admission, and “deep tissue injury”, a type of PrU resulting from pressure on muscle and fascia is thought to appear on the surface of the skin approximately 3 days following exposure to pressure.

A waiver of informed consent has been obtained from the Primary Investigator’s (PI) Institutional Review Board. Data on newly admitted residents with less than a 3-day stay will not be included in the analysis, because deep tissue injuries that result from pressure prior to admission may not be visible for up to 3 days after pressure exposure. Residents will also be excluded from the analysis if PrUs are present at baseline, PrU risk is severe (Braden score ≤ 9), or if the resident is cared for on a non-VE specialty surface, has “do not turn orders” present, or has an allergy to the adhesive used on the sensor. Residents assessed as being at severe risk of developing a PrU (estimated ≤ 10% per NH) will be excluded because they typically require specialty surfaces and individualized and frequent repositioning, and their health status is generally more unstable. Data on all other residents will be included, using an intention-to-treat approach. The target N for analysis is 951; we aim to enroll 1100 residents at baseline. Residents who are discharged, transferred, or die will be included in the intention-to-treat analysis.

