### Risk and challenges

This study design includes NHs with the same corporate management to ensure that the same standard-of-care protocols are in place in each NH. A major challenge for NH research is the potential for staff turnover. Using a successful strategy from our prior studies [31], we secured a written commitment that the study will continue even if there is a change in one or more of corporate administrative leaders for the NH system. We also have designed the study to be robust to staff turnover and potential staff resistance to a new repositioning schedule, by incorporating mandatory training with supplemental on-site instruction as needed and also incorporating training into the NH’s new staff orientations. Another potential challenge is staff inconsistency in implementing the repositioning protocol standard-of-care; consistency in repositioning is important to being able to subsequently demonstrate that the repositioning at the assigned interval actually occurred [33]. In fact, in practice, extended repositioning intervals already are thought to be extended beyond 2 h [34, 35] and there are longstanding concerns that nursing staff documentation may be unreliable for use as evidence of repositioning [20, 31, 36, 37]. The PM system monitoring capabilities will enable concerns about repositioning protocol compliance and documentation to be addressed via time-stamped tracking of identified position changes.

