**Fig. 3 Fig3:**
[figure not shown]
TEAM UP study high-level components diagram and key data sources

**Table 2 Tab2:** Summary of concepts and instruments / measurements used to collect data

Concept Measured	Measures / Instrumentation	Source (Fig. 3)
Cumulative incidence of (new) PrUs for pre-intervention (baseline) period	Cumulative Incidence rate = [(# of residents with 1 or more new PrUs during a 1-month period) ÷ (# of NH residents with 3 or more day stay)] × 100; calculated monthly to establish baseline over the 12-month period before each NH intervention begins.	• MDS 3.0 • NH self-report • EMR data extract
Cumulative incidence of (new) PrUs for intervention period	Cumulative Incidence rate = [(# of residents with 1 or more new PrUs during intervention period) ÷ (# of residents participating in intervention for 3 or more days)] × 100; calculated for the full 4-week intervention period.	• MDS 3.0 • NH self-report • EMR data extract
Braden Scale©	The Braden scale is being used per protocol by participating NHs to assess resident risk for PrUs at intervention start and weekly thereafter.	• EMR data extract
Repositioning frequency	The scheduled duration of time for a resident’s pressure exposure as reflected by the 2-, 3-, or 4-h time interval at which the resident is repositioned; each NH will be randomly assigned to one of the study’s 3 arms and will use a single NH-wide repositioning frequency.	• PMS Central Server containing Monitoring Management Software
Recorded repositioning frequency	The actual time interval at which repositioning occurs, as documented by the Leaf sensor; recorded in clock time hours and minutes, 24 h per day, from start to end of resident’s participation in the 4-week intervention. Repositioning activities of residents will be captured using the Patient Monitoring System; Admission, Discharge, Transfer (ADT) feed from NHS to Monitoring System enables a match for Study ID# to resident movement, which is required for resident tracking in the event of room change, discharge/readmission, or other events.	• PMS Central Server containing Monitoring Management Software
Repositioning protocol adherence: % agreement	Percentage of agreement between scheduled repositioning frequency and repositioning frequency recorded by wireless sensor: [(scheduled clock time - recorded clock time = # minutes difference) ÷ 60] × 100]; calculated for each resident’s repositioning episode.	• PMS Central Server containing Monitoring Management Software

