Because we will be examining PrU development from assessment to assessment, the rate of PrU incidence will be modeled as a binary outcome using repeated measures logistic regression and a specified working correlation matrix that models the correlation of responses within subjects. Full likelihood estimation methods are not appropriate for repeated measures logistic regression, so generalized estimating equations (GEEs) will be used instead with model fit assessed using the quasi-likelihood information criterion (QIC). Robust standard errors, clustered at the facility level, will be employed to account for covariance among residents within facilities over time. To test the robustness of models, we will also use non-linear mixed models using PROC GLIMMIX as another option for modeling the data (instead of GEEs using PROC GENMOD). With PROC GLIMMIX, we can use random effects to model the covariance rather than clustered standard errors. As predictors, we will include time-invariant resident characteristics, e.g., age, gender, Medicaid payer, and repositioning schedule, as well as time-varying characteristics, such as resident severity measure, risk level as determined by Braden Scale© score, staffing characteristics (e.g., number, mix, and turnover), and suggested MDS resident data elements as covariates. We may lag some time-varying resident characteristics by one assessment because we want to study the associations of repositioning time with PrU development, controlling for the starting point of the resident for that assessment interval. Interaction variables will be included in the predictor data set.

Residents without PrUs who drop out of the study after at least a three-day stay but before the conclusion of 4 weeks will be included in the analysis based on intent to treat. Residents who develop a Stage 3 or worse PrU, or deep purple discoloration, will be removed from the study per repositioning protocol, but will be considered a completed case if the ulcer developed on the coccyx, sacrum, trochanter or heel. Residents who develop ulcers on sites not thought to be influenced by bed position or limited mobility, or related to sitting, will continue to be followed for analysis, but will not be included in the NH-wide protocol.

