##### Statistical power.

According to previous research, the average PrU incidence rates range from 5.2–15%. At the time of study design, the nine NHs within the NHS were identified with the highest PrU incidence rates which averaged 9.2% (SD = 3.3%). In power analyses, we used 3.5% for PrU incidence as the expected rate for intervention since it is the highest rate found in the TURN study (for moderate-risk patients). The PrU incidence rates have been translated into an odds ratio of 0.38 (= 3.5%/9.2%) as the effect size to detect. For Aim 1, odds ratios from a logistic regression of PrU incidence rates in the three treatment arms (i.e., at 2-, 3-, and 4-h repositioning frequencies), controlling for risk level, are proposed to test the difference in PrU incidence rates between the 4-h arm and the 2-h arm as well as between the 4-h arm and the 3-h arm at 4 weeks; we are assuming that the distance between the 2-h arm and the TURN 3-h odds ratio will be larger. A sample size of *N* = 951 (*n* = 317 for each arm) will be required to detect an odds ratio of .38 with a power of 0.95 at a one-tailed significance level of α = 0.05, according to G*Power. We are using a power of 0.95 instead of the conventional power of 0.80 to ensure that we will have a smaller Type II error to test the hypothesis of no-group difference that we expect to fail to reject. We are using a one-tailed test since we are only interested in determining whether the PrU rate is higher for assigned repositioning intervals longer than the current 2-h standard practice.. For Aim 2, GEE is proposed. A sample size of *n* = 114 for each group (total *N* = 342) will be required to detect an effect size of 5.7% (= 9.2% - 3.5%) with a power of 0.80 at a one-tailed significance level of α = 0.05, using the algorithms GEESIZE developed by Dahmen, et al., on an autoregressive structure for residual correlations [48]. Since the nine NHs will be randomly assigned to the three treatment arms, risk level will be the only potential covariate to be controlled in the models, and this is already considered in the power analyses. Therefore, we will target a sample size of *N* = 951 (the larger of the two required sample sizes) for both aims while taking into account potential losses due to turnover, attrition, and exclusion criteria. While this proposed study may look like a non-inferiority or equivalence trial, we will run regular one-tailed superiority tests, because (as noted earlier) we are only interested in examining whether or not the PrU rate is higher for less frequent repositioning than for the standard 2-h repositioning. (We assume that 2-h repositioning was followed to produce the 9.2% average PrU incidence rate across our 9 study NHs, because that is the current standard of care). Also, according to Snapinn [49], non-inferiority trials have many controversial assumptions and limitations that need to be made or addressed, and that is beyond the control of our study. For incidence, it is difficult to specify a non-inferiority margin for PrU rates. Instead, we will test the hypothesis of no group-difference by examining whether the 95% confidence intervals of the odds ratios (for Aim 1) or the PrU rates (for Aim 2) of the two pairs of compared groups (e.g., 4-h arm vs. 2-h arm and 4-h arm vs. 3-h arm) overlap. If the confidence intervals do overlap, the hypothesis for no-group difference will be confirmed.

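### No difference would be confirmed on intention-to-treat by assigned interval, with no PrU analysis clearly committed to the delivered interval that the sensors record

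*Protocol article*

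**What the plan says.** **Conclusion sought.** The Statistical power section sets power at 0.95 "to test the hypothesis of no-group difference that we expect to fail to reject". It declines a margin because "it is difficult to specify a non-inferiority margin for PrU rates", and then fixes the rule: "If the confidence intervals do overlap, the hypothesis for no-group difference will be confirmed". The Quantitative analyses section gives the same rule for the PrU rates against the 2-h arm.

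**Analysis basis.** After the listed exclusions, Resident sample says: "Data on all other residents will be included, using an intention-to-treat approach". Quantitative analyses adds that residents who leave after at least three days but "before the conclusion of 4 weeks will be included in the analysis based on intent to treat". The repositioning schedule enters the outcome model as a time-invariant resident characteristic, that is, as assigned.

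**Departures from assignment.** Under Methods, residents may refuse the sensor and may decline to move when prompted. Under NH sample, they may "request a more frequent repositioning interval". Risk and challenges names staff inconsistency and says that in practice "extended repositioning intervals already are thought to be extended beyond 2 h".

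**Delivered interval.** Table 2 defines recorded repositioning frequency as "The actual time interval at which repositioning occurs, as documented by the Leaf sensor", and also defines a percentage-agreement measure. Resident-level data adds the percentage of on-time turns while the sensor is worn. The stated uses are adherence, fidelity and cost; the only sensitivity analysis said to use observed repositioning times is the one for the cost-effectiveness ratios.

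**The concern.** In a trial that sets out to find a difference, intention-to-treat is cautious because non-adherence usually shrinks the effect. Here the expected and desired result is no difference, so the same shrinkage helps the conclusion. If 2-h residents are turned late and some 4-h residents are turned more often, the arms receive more similar care and their PrU rates move closer. The decision rule cannot tell this apart from longer intervals truly being as safe.

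At stake is a statement about extending the repositioning interval that could partly reflect weak delivery. The data needed to judge that are collected, and the cost results are to be tested against observed repositioning times, but no corresponding check on PrU incidence is clearly promised.

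**Working it through.** **1. The plan's own figure.** Inputs from Statistical power: rates 9.2% and 3.5%, odds ratio taken as 0.38, one-tailed α = 0.05, power 0.95, N = 951 (317 per arm). The standard logistic-regression formula with a binary covariate is

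N = [z(α)·√(P(1−P)/B) + z(β)·√(P1(1−P1) + P2(1−P2)(1−B)/B)]² / [(P1−P2)²(1−B)].

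With P1 = 0.092, P2 = 0.0371 (from odds ratio 0.38), B = 1/3 and P = (2/3)(0.092) + (1/3)(0.0371) = 0.0737, N = 963. That is within about 1% of 951, and power at 951 is 0.948. So 951 reproduces as a total for one arm against the other two. For a pairwise contrast at 317 per arm, power is lower (step 2).

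**2. Pairwise power with full adherence.** Power = Φ[(d − 1.645·s0)/s1].

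- d = 0.092 − 0.035 = 0.057; mean rate 0.0635
- s0 = √(2 × 0.0635 × 0.9365/317) = 0.01937
- s1 = √((0.092 × 0.908 + 0.035 × 0.965)/317) = 0.01924
- (0.057 − 1.645 × 0.01937)/0.01924 = 1.307, so power = 0.904

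**3. Dilution (assumed).** The article gives no adherence rate. Let a share m of residents in each arm in effect receive the midpoint, with a rate of 6.35%. The higher rate becomes 9.2% − 2.85m points and the lower 3.5% + 2.85m points, so d = 5.7(1 − m) points. The mean rate, and hence s0, is unchanged.

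**4. The overlap rule.** For each pair of rates I simulated two arms of 317 (400,000 runs), formed separate Wilson 95% intervals for the two rates, and counted how often they overlap.

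| m | Higher rate | Lower rate | d (points) | z | One-tailed power | Intervals overlap |
|---|---|---|---|---|---|---|
| 0% | 9.20% | 3.50% | 5.70 | 1.307 | 0.90 | 42% |
| 20% | 8.63% | 4.07% | 4.56 | 0.712 | 0.76 | 67% |
| 30% | 8.35% | 4.36% | 3.99 | 0.416 | 0.66 | 77% |
| 40% | 8.06% | 4.64% | 3.42 | 0.121 | 0.55 | 85% |

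**5. A second dilution pattern.** If only the higher-rate arm moves towards the other, with a share of 20% or 40% in effect receiving the comparator's interval, power is 0.79 or 0.62 and overlap occurs in 63% or 81%. The pattern is the same.

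**6. When the arms would not converge.** If every arm ran late by the same proportion, say 25% (an assumption), the delivered intervals would be 2.5, 3.75 and 5 h. The 2-h to 4-h gap would be 2.5 h, not smaller.

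**Limits of the arithmetic.** Giving the higher rate to the longer-interval arm is illustrative, because the article ties 9.2% to current 2-h care. Clustering is ignored; it would lower power further. For Aim 1, Statistical power words the overlap in terms of odds-ratio intervals; the simulation uses rate intervals, as in Quantitative analyses.

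**The case against.** The strongest reply is that intention-to-treat is the right primary basis, and that supportive analysis sets are commonly left to an analysis plan that is not shown. A reader might infer that intention-to-treat is an error here, or that no other analysis exists. The document supports neither: it does not exclude further analyses. What stands is that this article itself fixes the conclusion. Overlap alone confirms no difference, and as written no finding about delivery can alter or qualify that.

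Three further readings go too far.

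- **That the sensor record serves only to describe adherence.** It also feeds the labor cost and the cost-effectiveness sensitivity analysis. Aim 1 says the monitoring system will be used to determine movement, and Quantitative analyses speaks of associations with repositioning time. The last two are ambiguous, but they are not adherence description.
- **That the article forecasts convergence in both arms.** The remark about intervals beyond 2 h describes existing practice. Cueing, training, champions and observation are there to correct it. The right to ask for more frequent turning comes with no predicted rate.
- **That a false finding of no difference rises from 10% to 24–45%.** Those figures are one minus one-tailed power. The article's rule is interval overlap, which gives about 42% rising to 67–85% under the same assumptions, and the 42% owes nothing to adherence.

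**Conclusion.** The point holds in a limited form. The article names only intention-to-treat by assigned schedule, seeks to confirm no difference, acknowledges routes by which delivery may depart from assignment, and collects the delivered interval without clearly committing any PrU analysis to it. Poor separation of the arms could therefore be reported as no difference.

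Under the assumed 20–40% shares, one-tailed power falls from 0.90 to 0.76–0.55, and the overlap rule would confirm no difference in about 67–85% of trials, against 42% with full adherence. Only the rise above 42% belongs to this point; the baseline is the fault of an overlap rule without a margin and needs its own correction. The size rests on assumed shares, on illustrative rates and on no clustering. The direction is likely, because late turns in the 2-h arm and extra turns in the 4-h arm both pull the arms together. It is not certain, because equal lateness would not, and the cueing system may keep drift small.

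**What to change.** Keep intention-to-treat primary for Aim 1. Prespecify a supportive PrU analysis by sensor-recorded interval in two forms:

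- the Aim 1 comparison among residents whose recorded interval lies within a prespecified tolerance of assignment;
- a model with recorded interval as a continuous exposure.

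Adjust both for baseline and time-varying Braden risk and for medical severity, which the article already plans to model. Report the result, with adherence and the distribution of delivered intervals by arm, beside the primary result. State in advance that any claim of no difference will be qualified if delivered intervals were not well separated or the supportive result disagrees.

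Do not make it a formal gate. Adherence is not random: residents who are turned more or less often may differ in risk, and those who refuse the sensor are missing. The analysis can inform the reading of the primary result but cannot overrule it.

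The cost is analyst time on data already collected. The article reports three of nine homes completed, so at that stage the analysis could still be fixed before the outcome comparison.
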